**Methods:**

We will recruit 80 adult patients who have been diagnosed with a FEP, received antipsychotic medication at Butabika Hospital and reside within 21km from the Hospital. Trained village health team (VHTs) members will deliver 6 psycho-education sessions to 40 participants and their family members (intervention arm). Participants in the control arm (n = 40) will receive routine care. We will document how feasible it will be to recruit and retain participants over 24 weeks and document the preliminary efficacy of the intervention on illness self-management, stigma, adherence to medications and severity of symptoms.

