### Sample size estimation

Being a study assessing feasibility of recruitment as a primary outcome, we have not conduced a formal sample size and power calculation. Rather, we have considered that recruiting 70% of potentially eligible participants over a 20-week period and retaining 80% of recruited participants will provide us with adequate data that will be needed in recruiting participants for a powered RCT.

In 2018 [41], a total of 43,870 individuals accessed care at the hospital, 60% (26,322) of them were diagnosed with psychotic disorders, approximately 20% (5,264) of the 26,322 patients with psychosis presented for the first time (potential cases of FEP). Thus, the number of participants who are eligible for recruitment is approximate 440 per month. Close to 20% of the Ugandan population lives within the central districts from where we intend to recruit participants—we anticipate having 88 patients (with psychosis) eligible for recruitment per week. However, a significant proportion of patients present with a psychosis resulting from substance use. We anticipate that approximately 40% of the 88 patients would be eligible as per criteria described below. Thus, we will have approximately 32 participants eligible for recruitment per week with a recruitment target of 24 of the 32 participants per week. We will document what proportion of this figure is attained.

With a sample size of 80 participants, we will be able to conduct preliminary analyses to detect modest significant differences (5% increase in mean scores) in illness self-management and adherence as well as a 5% reduction in mean stigma and symptom severity. We will use this data to generate an effect size that can be used in a sample size estimation of a powered RCT.

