#### Random sequence allocation

We will use a simple random technique to randomize participants. Random numbers that determine which study arm the participant will be in will be generated by an independent statistician who will not be part of the study team.

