### Data analysis plans

We will report the duration of recruiting participants and the proportion of eligible patients who get recruited. We will compare the demographic parameters (age, gender, education status) as well as disease severity. We will compare the proportion of participants who are retained in the study at week 4, 12 and 24 as well as mean differences in adherence, stigma, illness management ability and symptom severity (PANSS or YMRS) scores between the intervention and control arms. We will use the Bonferroni approach to correct for multiple comparisons.

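### The claim that 80 participants can detect a 5% difference in mean scores has no stated basis and holds only if the SD is about 7–8% of the mean or less; the pilot's observed effect size is also too imprecise to size the powered RCT

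*Protocol article*

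**What the plan says.** All of the sample size statements are in the protocol article, Sample size estimation. The section first says that, because feasibility is primary, "we have not conduced a formal sample size and power calculation". It then makes a statement about statistical performance: "With a sample size of 80 participants", the authors write, "we will be able to conduct preliminary analyses to detect modest significant differences (5% increase in mean scores" for illness self-management and adherence, together with 5% reductions in mean stigma and symptom severity. No SD, mean, significance level, sidedness or power accompanies this. The next sentence reads: "We will use this data to generate an effect size that can be used in a sample size estimation of a powered RCT".

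The abstract gives the arms as 40 and 40: the village health team will "deliver 6 psycho-education sessions to 40 participants and their family members (intervention arm", and "Participants in the control arm (n = 40) will receive routine care". The Hypothesis section expects 80% of the sample to be retained for 24 weeks. The abstract and Data analysis plans set between-arm comparisons of adherence, stigma, illness management and symptom severity at weeks 4, 12 and 24, and add: "We will use the Bonferroni approach to correct for multiple comparisons". The number of comparisons in the correction is not given.

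**The concern.** A detectable difference cannot be stated without an SD or a power calculation, and the section offers neither. A percentage of the mean says nothing about detectability until it is set against the spread of the scores. With about 40 per arm, a two-arm comparison of means detects effects of well over half an SD, so 5% of a mean is within reach only for scores that vary very little.

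Two uses of the trial depend on this. First, a reader who takes the sentence at face value could treat a non-significant result as evidence against a 5% effect when the trial had little chance of finding one. Second, the section offers the pilot's effect size as an input to the next trial's sample size. If that estimate is mostly noise, the main trial may be far too small, far too large, or dropped without good reason.

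**Working it through.** **Inputs from the protocol article.** 80 participants, 40 per arm; 80% retention at 24 weeks, so 0.80 × 40 = 32 per arm; four outcome domains; three follow-up visits; Bonferroni. Allocation is by simple randomization ("We will use a simple random technique to randomize participants"), so exactly 40/40 is not guaranteed. A split as uneven as 31/49 would raise the standard error by under 3% (√(1/31 + 1/49) = 0.2295 against √(2/40) = 0.2236), so this is ignored.

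**Assumptions, because the article gives no values.** Two-sided alpha 0.05; 80% power; Bonferroni family of 1, 4 (outcomes) or 12 (4 outcomes × 3 visits); SD/mean from 5% to 30%.

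**The plan's own figure** cannot be reproduced, because its inputs are not given. The statement can only be inverted to find what it requires.

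**Step 1: detectable standardized difference.** The normal approximation is d = (z for alpha + z for power) × √(2/n). With n = 40: (1.960 + 0.842) × 0.2236 = 0.626. With n = 32: 2.802 × 0.25 = 0.700. The two-sample t-test (noncentral t, 2n − 2 df) gives slightly larger values, used from here on. The last two columns are 0.05/d, the largest SD/mean at which 5% of the mean is detectable.

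| Tests in family | d, 40 per arm | d, 32 per arm | Largest SD/mean, 40 per arm | Largest SD/mean, 32 per arm |
|---|---|---|---|---|
| 1 | 0.634 | 0.711 | 7.9% | 7.0% |
| 4 | 0.762 | 0.856 | 6.6% | 5.8% |
| 12 | 0.851 | 0.959 | 5.9% | 5.2% |

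**Step 2: power for a 5% difference**, with d = 0.05/(SD/mean).

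| SD/mean (assumed) | d | 40 per arm, 1 test | 32 per arm, 1 test | 40 per arm, 12 tests | 32 per arm, 12 tests |
|---|---|---|---|---|---|
| 5% | 1.00 | 99% | 98% | 93% | 84% |
| 10% | 0.50 | 60% | 50% | 25% | 18% |
| 20% | 0.25 | 20% | 17% | 4% | 3% |
| 30% | 0.17 | 11% | 10% | 2% | 1% |

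At SD/mean of 20%, 80% power without correction needs 2 × 2.802² / 0.25² ≈ 252 per arm.

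**Step 3: symptom severity.** The Data collection section uses YMRS for bipolar illness and PANSS for schizophrenia spectrum disorders, so each scale covers only part of the sample. If a scale covered half (assumption: 20 per arm), the detectable d would be 0.91 and the limit on SD/mean 0.05/0.91 = 5.5%, before any correction.

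**Step 4: precision of the pilot effect size.** SE(d) = √(2/n + d²/(4n)). For d = 0.3: √(0.0625 + 0.0007) = 0.251 with 32 per arm, and 0.225 with 40. The 95% CI is therefore about ±0.49 or ±0.44. An observed 0.30 with 32 per arm runs from −0.19 to 0.79. The size of an RCT at 80% power is 2 × 2.802² / d² = 15.70/d² per arm: 175 at 0.30, 25 at 0.79, and no finite number at the lower limit.

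**Step 5: consequence for the later RCT, if the true d is 0.3 (assumption) and 32 per arm are analysed.** Among pilots with a positive estimate, simulation gives a derived size with 10th and 90th percentiles of about 37 and 1,800 per arm. An RCT has under 50% power when its size is below 2 × 1.96² / 0.3² = 85 per arm, which happens when the observed d exceeds 0.3 × 2.802/1.960 = 0.429. That probability is P(Z > (0.429 − 0.3)/0.251) = 0.30. A positive estimate has probability 0.88, so the share is 0.30/0.88, about 35% (31% of all pilots). With 40 per arm, the range is about 43 to 1,700 and the share about 32%.

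**The case against.** The strongest reply is that this is a feasibility pilot. The 80 are not derived from the 5% statement, efficacy is called preliminary throughout, the article admits that no power calculation was done, and a powered trial is to follow. All of that stands. The trial does not need to be powered for efficacy, and nothing here questions the choice of 80. But it is a reason to withdraw the performance claim, not to keep it.

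Three stronger readings are tempting, and the documents do not support them.

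- **That the 5% claim is false.** No SD or mean is given, so it cannot be disproved. At SD/mean of 5% it would be true, with 98–99% power uncorrected.
- **That the plan fixes Bonferroni over 12 tests.** It names the method only; the family may properly be set in an analysis plan that is not shown. The figures for 4 and 12 tests are conditional. The uncorrected limit of 7–8% does not depend on them.
- **That the next trial will be sized on the pilot's point estimate alone.** The article says the effect size can be used, not that nothing else will be.

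It is also fair that 32 per arm is the week-24 figure and that more may remain at weeks 4 and 12, which is why 40 per arm is shown alongside. Kinder analyses help only modestly. A one-sided 0.05 test with 40 per arm raises the limit to about 9%. Baseline adjustment with an assumed correlation of 0.5 to 0.7 raises it to about 9–11%. However, Table 1 marks the adherence and illness management measures as not taken at baseline, so as that table stands the adjustment is not available for the two outcomes named for a 5% increase.

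**Conclusion.** The point holds in this form: the 5% claim is unsupported, and cannot be met at 80% power unless SD/mean is about 7–8% or less, or about 5–7% if Bonferroni covers 4 or 12 tests. With 32 per arm, uncorrected power for a 5% difference falls from 98% to 50%, 17% and 10% as SD/mean goes from 5% to 10%, 20% and 30%. The claim is least credible for symptom severity, which is divided between two scales and measured in patients whose active symptoms have already resolved, so that 5% of the mean is likely to be a small change.

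The imprecision of the effect size does not depend on SD/mean: ±0.44 to ±0.49 SD follows from the sample size alone. The spread of derived RCT sizes, and the 35% of those trials that would have under 50% power, rest on the assumed true d of 0.3.

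The primary feasibility objective is untouched. What changes is what the pilot may conclude about efficacy and what it may pass on to the powered trial.

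**What to change.** In Sample size estimation, make three changes.

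1. Replace the 5% claim with the standardized difference that the design can detect: 0.63 SD with 40 per arm and 0.71 SD with 32 per arm, at two-sided 0.05 and 80% power. Add that it is larger after Bonferroni (0.76–0.86 SD for 4 tests, 0.85–0.96 for 12), quoting the figure for whichever family is adopted. If the authors wish to keep a percentage, they should give the means and SDs that justify it, outcome by outcome.
2. State that efficacy results will be reported as estimates with 95% CIs, so that a non-significant result is not read as excluding a useful effect.
3. Replace the sentence on the effect size: the powered RCT will be sized on a pre-stated smallest worthwhile difference, with SD, recruitment, uptake and retention taken from the pilot, and not on its observed effect size. The pilot can supply an SD with useful precision: with 62 degrees of freedom its relative standard error is about 1/√(2 × 62) = 9% under normality, or about 18% on the derived sample size.

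The cost is wording and a less favourable stated figure. No patients, visits or measurements are added.

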### Data collection methods

#### Training

RAs and VHTs will each undergo 4-day’s training in the study procedures.

#### Random sequence allocation

We will use a simple random technique to randomize participants. Random numbers that determine which study arm the participant will be in will be generated by an independent statistician who will not be part of the study team.

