#### Data collection

The health care providers based in the wards from where we will collect data will be informed about the study. They will identify patients who may be eligible and refer them to the RA for a second round of eligibility screening. The RAs shall provide potential participants with information about the study, obtain written informed consent, then administer the University of California, San Diego Brief Assessment of Capacity to Consent (UBACC) [42] to assess participant comprehension of the consent process.

RA’s will administer a) standardized questionnaire to collect demographic and clinical variables (age, gender, address, education, date of symptom onset) from the patients. We will collect demographic information in the form of age, gender, address and education from care givers. b) Feasibility measures (number of eligible participants who accept to enroll in the study, number of participants who are retained in care over study duration, number of participants who adhere to prescribed intervention, duration of recruitment of participants, reasons for decline to enroll in the study as well as reasons for dropping out of the study), c) MINI to confirm a diagnosis, d) Young Mania Rating Scale (YMRS) [43] for individuals with bipolar illness or Positive and Negative Symptoms of Schizophrenia Scale (PANSS) [44] for individuals with schizophrenia spectrum disorders to assess symptom severity e) World Health Organization Disability Assessment Schedule, f) Internalized Stigma of Mental Illness scale to assess for stigma, g) a medication adherence measure to assess for adherence h) Illness Management and Recovery (IMR) [45] scale to document the ability of patients to manage their illness and (i) care giver burden using the short version of the burden scale for care givers (BSFC) [46].

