#### Blinding participants and RA to the study arm

Participants will be randomly assigned to the study arms. The RA and participants will all be blinded to the study arm they will be allocated before consent. VHTs will deliver 6 psycho-education sessions (1 per month) to participants in intervention arm and their family members at the participant’s residence. The PI and RAs will sit in some of the sessions during the first 2–3 sessions of data collection to ensure fidelity to the manual. We will conduct 5 exit focus group discussions with patients and family members to assess acceptability to the use of the manual. Participants in the control arm will get usual treatment. RA’s will schedule participants from both arms for an assessment using the same instruments at weeks 4, 12 and 24 at the clinic. We will have a separate set of RA’s for the intervention arm and another for the control arm to ensure blinding of the RA.

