### The intervention

After discharge, the program manager will link the participants with a VHT nearest to them. The participants (randomized to the intervention arm) will be informed during the consent procedure that they will undergo 6 psycho-education sessions (1 per month) together with a family member at the participant’s residence. The VHTs and participants will meet and schedule appointments for the next engagements. This shall be done on a case by case basis. Some psycho-education sessions could take place in the patient’s residence, others in the nearest public space (school or church or mosque compounds). We will document where the majority of these sessions happen. This will help us document feasibility. The PI and RAs will sit in some of the sessions during the pilot phase of data collection to ensure fidelity to the manual.

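### Simple randomisation of 80 will seldom give the stated 40 and 40 and leaves diagnosis to chance; concealed blocks stratified by diagnosis are a cheap improvement, and the consent wording needs reconciling

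*Protocol article*

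**What the plan says.** **Allocation.** Under Random sequence allocation: "We will use a simple random technique to randomize participants". The same section adds: "Random numbers that determine which study arm the participant will be in will be generated by an independent statistician". Neither blocks, strata nor a list with fixed totals is mentioned anywhere in the article.

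**Arm sizes.** The abstract's Methods paragraph has village health team members "deliver 6 psycho-education sessions to 40 participants and their family members (intervention arm"), and then: "Participants in the control arm (n = 40) will receive routine care". Sample size estimation gives only the total of 80 and says "we have not conduced a formal sample size and power calculation".

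**Diagnosis and outcome scale.** The Introduction defines psychosis to include schizophrenia-spectrum, brief psychotic and bipolar disorders. Data collection assigns the "Young Mania Rating Scale (YMRS) [43] for individuals with bipolar illness or Positive and Negative Symptoms of Schizophrenia Scale (PANSS") for schizophrenia-spectrum disorders. Data analysis plans compares mean PANSS or YMRS scores between arms, along with adherence, stigma and illness management. Eligibility criteria has the diagnosis confirmed by M.I.N.I interview, so it can be known before allocation.

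**Baseline measures.** Table 1 marks the MARS (adherence) and the IMR (illness management) as not given at baseline and does not list the stigma scale. YMRS/PANSS is given at baseline.

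**Consent.** Under Blinding participants and RA to the study arm, research assistants and participants are "blinded to the study arm they will be allocated before consent". Under The intervention, participants described in brackets as randomised to the intervention arm "will be informed during the consent procedure that they will undergo 6 psycho-education sessions (1 per month").

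**The concern.** Three things are at stake, in rising order of importance.

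1. The abstract's arm sizes and the stated method do not fit together. An unrestricted sequence has random arm sizes; 40 is only their expected value.
2. The trial mixes diagnoses, and diagnosis decides the severity scale. Each severity comparison therefore uses only part of the 80, and nothing keeps that part evenly split. For the outcomes scored on one scale in everyone, diagnosis may be prognostic, and an uneven mix adds noise to estimates that are meant to supply the effect size for a powered trial.
3. If arm were known during consent, willingness to enrol could depend on arm. The proportion of eligible patients recruited is a primary feasibility measure, so that result and the comparability of the arms would both be affected.

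**Working it through.** **Inputs.** Total 80 and 40 per arm (abstract), implying 1:1; simple randomisation (Random sequence allocation). The bipolar share *p* is not in the document, so I take 20% to 50% as an assumption and show the range.

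**Arm sizes.** There is no sample size calculation to reproduce; 40 is 80 × 0.5. With X ~ Binomial(80, 0.5):

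- P(X = 40) = C(80,40)/2^80 = 0.089
- P(45/35 or worse) = 2·P(X ≥ 45) = 0.314
- P(50/30 or worse) = 2·P(X ≥ 50) = 0.033

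**Cost in precision.** Efficiency relative to equal arms is 4·n1·n2/N². At 45/35 it is 4·45·35/6400 = 0.984; at 50/30 it is 4·50·30/6400 = 0.9375. Its expectation is 4·(80·40 − (40² + 20))/6400 = 0.9875, a loss of 1.25%.

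**Diagnosis mix.** The difference in bipolar share between arms has mean 0 and, at 40/40, SD √(p(1−p)·2/40): 0.089 at p = 0.2 and 0.112 at p = 0.5. Letting both arm size and diagnosis vary, as under simple randomisation:

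| Assumed bipolar share | Gap ≥10 points | Gap ≥15 points | Gap ≥20 points |
|---|---|---|---|
| 20% | 27% | 10% | 3% |
| 30% | 34% | 15% | 5% |
| 40% | 37% | 18% | 7% |
| 50% | 38% | 19% | 8% |

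Fixing the arms at 40 each does not help. With two independent Binomial(40, p) counts, P(|difference| ≥ 4) is 33% at p = 0.2 and 43% at p = 0.5. These are higher because a gap of exactly 4 in 40 counts as 10 points.

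**What a gap does.**

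- *Outcomes on one common scale:* if bipolar and other patients differ by D standard deviations, a 10-point gap moves the unadjusted arm difference by 0.10·D. With D = 1 (illustrative) that is 0.10 SD, against a standard error of √(1/40 + 1/40) = 0.22 SD. It is noticeable but not dominant.
- *Severity, compared within each scale:* a gap changes only the subgroup sizes. A bipolar group of 16 (20% of 80) splits 2:1 or worse in 21% of trials, and one of 24 (30%) in 15%. At 2:1, efficiency within that group is 4·(2/3)·(1/3) = 0.89.

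**After the change.** Under permuted blocks of 4 and 6 in two diagnosis strata, an unfinished block of 6 can leave a stratum at most 3 out. The worst overall split is therefore 43/37 and the worst diagnosis gap 3/40 = 7.5 points. Simulation (20,000 trials for each assumed share) reached both limits, gave exactly 40/40 in about 55% of trials, and never gave a 10-point gap.

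**Consent.** Set side by side, the Blinding section puts knowledge of arm after consent, while The intervention section, read literally, has people already in the intervention arm being told of their sessions during consent. Both cannot describe the same sequence.

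**The case against.** - **Arm sizes are harmless.** Feasibility is primary, no power calculation is claimed, and uneven arms cost about 1%. This stands. The per-arm figures quoted come from the abstract and read naturally as targets, and the phrase about a simple technique might loosely mean a shuffled list with 40 per arm. If so, the article should say so; diagnosis would still be uncontrolled.
- **There is no bias.** A reader might infer that an uneven diagnosis mix biases the comparisons, above all severity. The document does not support that. Simple randomisation balances diagnosis in expectation, and a gap below 10 points is the usual result. Nothing says that PANSS and YMRS are pooled; compared separately, an uneven mix costs precision within a subgroup and does not distort the contrast. Severity is also one of four secondary clinical outcomes.
- **Blocks are not free.** This also stands. The intervention is unmasked and each arm has its own research assistants, so blocks make the next allocation easier to guess. Nor do stratified blocks guarantee 40/40.
- **The consent point is separate.** It is unrelated to the choice between simple and blocked randomisation. The bracketed phrase may only identify who would receive the sessions described to every candidate. A reader might infer that consent will in fact depend on arm; the Blinding section says otherwise, so the text shows a conflict of wording and not an established flaw in conduct.

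Against this, Table 1 as printed gives no baseline MARS or IMR, so chance differences on those outcomes cannot be adjusted for through the baseline score. That makes control of a known factor at allocation more worthwhile.

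**Conclusion.** The point holds in a limited form. Simple randomisation and the stated 40 and 40 agree in about 9% of trials, which is an inconsistency with little statistical cost. Diagnosis is left to chance, with a gap of 10 points or more in about 27% to 38% of trials if 20% to 50% of participants are bipolar. That range rests on an assumed share, because none is given. The consequence is extra noise in small comparisons of secondary outcomes, not bias and not a material loss of power from unequal arms. The argument about missing baseline scores depends on Table 1 being right as printed. The two statements on when arm becomes known conflict as worded and touch a primary outcome, so they need reconciling whichever randomisation method is kept.

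**What to change.** 1. Have the independent statistician issue a concealed list in permuted blocks of varying size (for example 4 and 6), stratified by baseline M.I.N.I diagnosis, bipolar versus other. Include the stratum in the analysis.
2. Describe 40 per arm as approximate. If simple randomisation or a shuffled 40/40 list is what is meant, say which, and still adjust for diagnosis.
3. Reword The intervention section to agree with the Blinding section: allocation is revealed only after consent, UBACC and baseline assessment, and everyone receives the same consent information about both arms.

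**Cost.** A new list and a few sentences of text. The M.I.N.I diagnosis must be fixed before allocation. Allocation becomes slightly more predictable, which varying and undisclosed block sizes keep small.
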